#### IKMT of the Core Muscle Group

IKMT combines the methodological strengths of isometric and isotonic assessments, allowing for precise quantification of muscle strength with excellent reproducibility and reliability [57]. Considering the critical role of core musculature in respiratory assistance, IKMT-based evaluation of core muscle function offers valuable insights into respiratory muscle status. In this trial, an IKANG multijoint muscle training and testing system (NX, A8-3, CHN) will be used to perform isometric assessments of trunk core muscles to examine functional changes induced by intervention. In accordance with established studies [34,58-61], the isometric contraction mode was applied. During testing, participants will be seated in the standardized position recommended by the manufacturer, with the trunk flexion–extension axis aligned at the level of the greater trochanter. The pelvis, lower extremities, and shoulders will be firmly stabilized with fixation devices. Standardized calibration will be performed before testing, and all assessments will be conducted by the same evaluator within a consistent time frame to reduce variability. Each participant will complete three warm-up repetitions followed by five maximal-effort isometric contractions for both trunk flexion and extension. The primary outcome variables include peak torque, peak torque to body weight ratio, time to peak torque, and average power. The IKMT of the core muscle group is illustrated in Figure 4. All measurements will be obtained in week 0 and week 13.

**Figure 4. F4:**
[figure not shown]
Isokinetic muscle strength test of the core muscle group. Participants were seated with the trunk flexion-extension axis aligned with the level of the greater trochanter. The pelvis, lower extremities, and shoulders were stabilized during testing. Isometric trunk flexion and extension strength were assessed using the IKANG multijoint muscle training and testing system.

### Exploratory Outcome Measures

#### Overview

We consider gait and plantar pressure parameters as exploratory outcomes. These measures do more than just provide descriptive biomechanical data—they also help us rule out a plausible alternative: that any improvement in 6MWT could be driven primarily by enhanced lower limb function rather than by respiratory muscle gains. Should these parameters show meaningful changes, we will include them as covariates in the 6MWT analysis, which allows us to tease out the independent contribution of respiratory muscle function.

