#### 6MWT

6MWT is a widely used method for evaluating exercise capacity in patients with respiratory disorders and for assessing the efficacy of clinical interventions. Previous studies [48,49] have demonstrated that the 6MWT serves as a valid and reliable measure of functional capacity and health-related quality of life in patients with COPD, while also providing an indicator of disease severity. Based on previous findings [37,38], the MCID for 6MWT ranges from 30 to 54 m, and the baseline SD is between 70 and 90 m. This study will use a 6MWT data acquisition system in combination with a dynamic vital signs monitor, CB200 (Contec), for testing. Participants will be instructed to walk back and forth along a 30-meter flat corridor at their maximum tolerable speed for six minutes. Distance markers will be placed every 5 meters to aid measurement. The recording device will capture the total walking distance as well as heart rate and oxygen saturation before and after the test. The 6MWT outcome will serve as a primary indicator of intervention efficacy, assessed in week 0 and week 13.

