#### Kinematics Test

The kinematic test uses optical, pressure, and other sensor technologies to quantitatively evaluate the activity of the human musculoskeletal system, thereby elucidating the biomechanical patterns of human movement. In this study, gait analysis and plantar pressure assessment will be conducted in patients with stable COPD to investigate lower limb functional improvements following Liuzijue exercise intervention.

A previous [62] study had demonstrated that gait analysis can sensitively reflect the disease status of patients with COPD and predict their functional prognosis. In this study, a joint motion function testing system (innoMotion, CHN) will be used in combination with a treadmill system (KPOWER, K153D-C-3, CHN) and dedicated gait analysis software (Xmotion, CHN) to evaluate gait characteristics before and after the intervention. The primary outcome measures include joint kinematics of the hip, knee, and ankle, as well as overall gait stability. Before testing, reflective markers will be attached to the participants’ waist, femur, tibia, and foot, after which they will stand on the treadmill. During the test, participants first walk forward at a speed of 3 km/h, and 15 seconds of gait data will be collected; they then walk backward at the same speed, and another 15 seconds of data will be recorded. The gait analysis is illustrated in Figure 5.

Plantar pressure assessment enables accurate evaluation of the medial longitudinal arch and the distribution of plantar forces during walking. Evidence suggests that patients with COPD may present with abnormal plantar pressure patterns, potentially contributing to a decline in quality of life [63]. In this study, a plantar pressure testing platform (Medtrack, CHN) in conjunction with the gait training and testing software (version 5.1.0.8) will be used for analysis. The system is used to record and evaluate the condition of the foot arch and the inversion/eversion curves, thereby assessing changes in plantar pressure before and after the Liuzijue exercise intervention. The plantar pressure testing is illustrated in Figure 6.

Both gait analysis and plantar pressure assessment will be performed in week 0 and week 13.

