### Statistical Analysis

Statistical analyses will be executed using SPSS (version 27.0), adhering to a two-sided significance threshold of *P*<.05 while reporting effect sizes and 95% CIs where appropriate. Baseline characteristics will be summarized solely through descriptive statistics without formal hypothesis testing, with continuous variables first evaluated for normality and homogeneity of variance to determine their presentation as either mean with SD or median with IQR.

Under an intention-to-treat framework encompassing all randomized participants, missing data patterns will be evaluated and addressed via multiple imputations, the robustness of which will be subsequently verified through sensitivity analyses including per-protocol and complete-case approaches. Primary outcomes will be modeled using linear mixed-effects specifications that will incorporate group, time, and their interaction as fixed effects alongside participant-level random intercepts to account for the repeated-measures design.

For continuous secondary outcomes, analysis of covariance adjusted for baseline values will be used where appropriate, whereas other continuous and categorical variables—the latter summarized as frequencies and percentages—will be scrutinized using parametric, nonparametric, chi-square, or Fisher exact tests depending on data distribution, with false discovery rate adjustments applied throughout to mitigate type I error inflation from multiple comparisons.

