Building upon this framework, this study further integrates static and dynamic sEMG together with IKMT to objectively characterize the functional properties of respiratory and core muscle groups. This approach aims to address a key limitation of previous COPD rehabilitation studies, in which the mechanisms underlying intervention effects—particularly those related to respiratory muscle function—have received relatively limited attention. Specifically, sEMG, as another primary outcome measure, can objectively and clearly reflect changes in respiratory muscle function in participants. In this study, both static and dynamic sEMG assessments will be performed to comprehensively evaluate respiratory muscle activation patterns under different conditions. Static sEMG will be applied to analyze muscle excitability and recruitment patterns of respiratory muscles at rest, whereas dynamic sEMG will be used to record muscle activation during movement [41-43]. Combined with IKMT of the core musculature, these assessments will enable quantitative evaluation of the strength and endurance of accessory respiratory muscles [57]. Through comprehensive multimodal analysis, the functional status and adaptive changes of respiration-related muscle groups can be more thoroughly elucidated, providing objective and reliable evidence for evaluating the mechanistic effects and long-term value of Liuzijue interventions.

In addition, a novel kinematic perspective will be introduced by incorporating gait analysis and plantar pressure assessment to systematically evaluate changes in lower-limb function. This strategy will help exclude potential confounding effects arising from muscular adaptations outside the respiratory system, thereby further strengthening the accuracy and internal validity of intervention effect determination [62,63].

The two coprimary outcomes in this study will serve distinct yet complementary purposes. The 6MWT is selected to capture clinically meaningful changes in functional exercise capacity, whereas sEMG provides a more direct assessment of neuromuscular activity in the respiratory muscles, thereby offering mechanistic insight into the intervention’s effects. Regarding sample size estimation, we based our calculations on the 6MWT, primarily because published data on sEMG responses to Liuzijue training in patients with COPD remain limited, precluding a reliable a priori estimate.

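### A conditional rule would adjust the coprimary 6MWT analysis for gait and plantar-pressure changes that arise after randomisation; it is not labelled supplementary and cannot isolate the respiratory-muscle effect

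*Protocol article*

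**What the plan says.** Under Exploratory Outcome Measures (Overview), the Protocol article gives the reason for measuring gait and plantar pressure: to rule out that "any improvement in 6MWT could be driven primarily by enhanced lower limb function rather than by respiratory muscle gains". It then commits to a rule: "Should these parameters show meaningful changes, we will include them as covariates in the 6MWT analysis". The purpose claimed for this adjustment is one of attribution; in the protocol's words, it is a step "which allows us to tease out the independent contribution of respiratory muscle function".

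Kinematics Test says that these measurements are made "to investigate lower limb functional improvements following Liuzijue exercise intervention", and fixes the timing: "Both gait analysis and plantar pressure assessment will be performed in week 0 and week 13".

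The 6MWT is one of two coprimary outcomes: "The 6MWT outcome will serve as a primary indicator of intervention efficacy, assessed in week 0 and week 13". Statistical Analysis says that the models for the primary outcomes will "incorporate group, time, and their interaction as fixed effects alongside participant-level random intercepts to account for the repeated-measures design". No gait or plantar-pressure covariate is listed there.

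In the Discussion (Principal Findings), the same idea returns as a strength of the design: "This strategy will help exclude potential confounding effects arising from muscular adaptations outside the respiratory system". The sentence goes on to credit the strategy with better internal validity.

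**The concern.** A change in gait can be known only from week-13 data. It is therefore a post-randomisation quantity, and the protocol itself expects that Liuzijue may alter it and that it may in turn alter walking distance. That is the definition of a possible mediator. In a randomised comparison, gait adaptation caused by the exercise is part of the treatment effect; it is not confounding.

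Three things follow.

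- If the rule governs the coprimary analysis, the quantity estimated is no longer the total effect of assignment to Liuzijue but an effect with the gait route removed.
- The rule depends on the results. It does not say which parameters count, how large a change is meaningful, or whether the change is within or between arms. Two 6MWT models are then possible, and the data decide between them.
- The stated aim is not reached on any reading. What is left after adjustment is everything that does not pass through the measured gait variables, such as general fitness, motivation, attention and respiratory muscle together. Gait is not randomised either, so any unmeasured cause shared by gait and walking distance biases what is left. Kinematics Test says that gait reflects disease status and predicts functional prognosis, which makes shared causes plausible.

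**Working it through.** The protocol gives no figure for this adjustment, so there is none to reproduce. The documents supply 54 m as the planned 6MWT difference and 32 per group before dropout (Sample Size Calculation). All other inputs are assumptions.

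**Set-up.** Let T be the total effect on 6MWT, a the shift in gait caused by treatment (in SD), b the metres of 6MWT per SD of gait, r the correlation of an unmeasured cause with gait, and u its effect on 6MWT in metres per SD.

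- True direct effect: D = T - a × b.
- Gait coefficient in the adjusted model: b + r × u.
- Adjusted group estimate: T - a × (b + r × u) = D - a × r × u.

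The term a × b is the change of estimand. The term a × r × u is bias.

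| T (m) | a | b | r, u | D (m) | Adjusted estimate (m) | Bias (m) |
|---|---|---|---|---|---|---|
| 54 | 0.5 | 10 | none | 49 | 54 - 0.5 × 10 = 49 | 0 |
| 54 | 0.5 | 40 | none | 34 | 54 - 0.5 × 40 = 34 | 0 |
| 54 | 0.5 | 40 | 0.25, 20 | 34 | 54 - 0.5 × 45 = 31.5 | -2.5 |
| 54 | 0.5 | 40 | 0.5, 40 | 34 | 54 - 0.5 × 60 = 24 | -10 |
| 0 | 0.5 | 0 | none | 0 | 0 | 0 |
| 0 | 0.5 | 0 | 0.5, 40 | 0 | 0 - 0.5 × 20 = -10 | -10 |
| 0 | 0.8 | 0 | 0.5, 40 | 0 | 0 - 0.8 × 20 = -16 | -16 |

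**Check by simulation** (32 per arm, linear models with and without gait, adjustment in every run). For rows 2, 4 and 6, the mean unadjusted estimates were 54.2, 53.5 and 0.1 m, and the adjusted ones 34.1, 23.7 and -9.8 m. For row 7, the adjusted mean was -16.0 m, and a true null was rejected in 12.1% of runs against 5.2% unadjusted.

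**Conditional use.** The rule applies only when triggered. Suppose that meaningful is taken as a significant gait difference between arms, which is an assumption. With a = 0.5 and 32 per arm, the standard error of the gait difference is √(2/32) = 0.25 SD, so the expected test statistic is 0.5/0.25 = 2.0 and the rule fires in about 50% of trials. When it does not fire, the mean gait difference is about 0.5 - 0.25 × 0.80 = 0.30 SD, and the unadjusted estimate is reported. The averages are then:

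- Row 2: unfired 34 + 40 × 0.30 = 46, so 0.5 × 34 + 0.5 × 46 = 40 m (simulated 39.6).
- Row 4: unfired 24 + 60 × 0.30 = 42, so 0.5 × 24 + 0.5 × 42 = 33 m (simulated 32.9).
- Row 6: unfired -10 + 20 × 0.30 = -4, so 0.5 × (-10) + 0.5 × (-4) = -7 m (simulated -6.8).

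Each average lies between the unadjusted and the always-adjusted value.

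**The case against.** The strongest reply is that the primary model stands in Statistical Analysis without these covariates, under intention-to-treat. The disputed sentence sits under exploratory outcomes and gives a mechanistic reason. It may describe an additional explanatory model, in which case the randomised comparison is untouched. This stands as a possible reading, so a reader who infers that the coprimary result will certainly be adjusted, or that randomisation no longer protects it, goes further than the text. But the sentence refers to the 6MWT analysis without any such limit, and an analyst who follows it literally would alter a coprimary result.

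A reader might also take the fall from 54 m to 34 m as bias. It is not: 34 m is the true direct effect in that scenario, and the model recovers it. Bias appears only when a shared cause is assumed, and so does the negative estimate under a true null. Nor do the figures suggest that a real 54 m benefit would typically change sign: no such scenario has a negative mean, and in a re-run of these scenarios only 3-4% of individual trials were negative.

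The inputs are open to challenge. Gait is tested at a fixed treadmill speed of 3 km/h, and plantar testing covers arch and inversion/eversion. A link of 40 m per SD, half of the 80 m planning SD, is strong for such measures. At 10 m per SD with no shared cause the estimate stays at 49 m, and with a 0.2 SD shift it is 54 - 0.2 × 10 = 52 m. The loss may be small.

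Finally, the sentence does not say whether baseline, week-13 or change values would enter. Baseline values alone would not be mediators, but they would not serve the stated purpose, and the trigger would still use week-13 data.

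**Conclusion.** The point holds as a fault in what the protocol states. It sets a data-triggered rule to adjust a coprimary outcome for possible mediators, does not label the result supplementary, and treats mediation as confounding. Which 6MWT model is primary cannot be settled from the text, so the sections must be reconciled. If the rule applies to the coprimary analysis, the estimand moves from the total to a direct effect. Even as a purely mechanistic analysis, it does not deliver the respiratory-muscle share that it promises.

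The size is unknown: it depends on how far Liuzijue shifts gait, how strongly gait drives 6MWT, and whether the two share unmeasured causes, none of which the documents give. Over the values for a true 54 m effect and a 0.5 SD shift, always adjusting moves the estimate to between 49 m and 34 m through change of estimand alone. The stronger shared cause takes off a further 10 m and the weaker one 2.5 m. Conditional use moves the averages part of the way back. The working uses a simple linear model in place of the planned mixed model, so the figures are illustrative.

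**What to change.** 1. Delete the conditional-covariate sentence. Alternatively, limit it to a separately labelled exploratory mediation analysis that names the gait and plantar-pressure parameters in advance, states its assumptions, and examines sensitivity to unmeasured mediator-outcome confounding. Say that this analysis cannot replace or modify the 6MWT result.
2. State that the 6MWT effect analysis is the model under Statistical Analysis, by randomised group, with pre-randomisation covariates only. Baseline gait may be included if named in advance.
3. Report week-13 gait and plantar pressure by arm as exploratory outcomes.
4. In the Discussion, soften the statement that the strategy helps to exclude confounding and strengthens internal validity; say that it describes possible lower-limb pathways.

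The cost is wording only, with no new data or visits. Analysis is planned for January 2027, so the change can be made and dated before results are seen.

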#### Kinematics Test

The kinematic test uses optical, pressure, and other sensor technologies to quantitatively evaluate the activity of the human musculoskeletal system, thereby elucidating the biomechanical patterns of human movement. In this study, gait analysis and plantar pressure assessment will be conducted in patients with stable COPD to investigate lower limb functional improvements following Liuzijue exercise intervention.

A previous [62] study had demonstrated that gait analysis can sensitively reflect the disease status of patients with COPD and predict their functional prognosis. In this study, a joint motion function testing system (innoMotion, CHN) will be used in combination with a treadmill system (KPOWER, K153D-C-3, CHN) and dedicated gait analysis software (Xmotion, CHN) to evaluate gait characteristics before and after the intervention. The primary outcome measures include joint kinematics of the hip, knee, and ankle, as well as overall gait stability. Before testing, reflective markers will be attached to the participants’ waist, femur, tibia, and foot, after which they will stand on the treadmill. During the test, participants first walk forward at a speed of 3 km/h, and 15 seconds of gait data will be collected; they then walk backward at the same speed, and another 15 seconds of data will be recorded. The gait analysis is illustrated in Figure 5.

Plantar pressure assessment enables accurate evaluation of the medial longitudinal arch and the distribution of plantar forces during walking. Evidence suggests that patients with COPD may present with abnormal plantar pressure patterns, potentially contributing to a decline in quality of life [63]. In this study, a plantar pressure testing platform (Medtrack, CHN) in conjunction with the gait training and testing software (version 5.1.0.8) will be used for analysis. The system is used to record and evaluate the condition of the foot arch and the inversion/eversion curves, thereby assessing changes in plantar pressure before and after the Liuzijue exercise intervention. The plantar pressure testing is illustrated in Figure 6.

Both gait analysis and plantar pressure assessment will be performed in week 0 and week 13.

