In addition to improving lung function, Liuzijue also exerts a positive effect on skeletal muscle, particularly the function of large muscle groups. Existing studies have shown that Liuzijue, through the pronunciation of the six characters “xu,” “he,” “hu,” “si,” “chui,” and “xi,” can simulate the physiological effects of pursed-lip breathing and diaphragmatic breathing, thereby effectively alleviating dyspnea in patients with COPD [24,30,31]. Moreover, the vocalization process during the practice prolongs exhalation time, which helps improve gas retention. Simultaneously, its coordinated limb movements constitute a low-intensity aerobic exercise model. Through the combined effects of rhythmic limb movement and large muscle group coordination training, it enhances the strength and endurance of major muscle groups such as the quadriceps and biceps [32]. However, despite the demonstrated benefits of Liuzijue in improving respiratory function and enhancing skeletal muscle strength, research on its direct effects on respiratory muscle function remains relatively limited and mostly confined to theoretical discussions. Existing studies [24,30-32] have primarily focused on improving core muscle function, with insufficient clinical evidence regarding its specific impact on respiratory muscle groups such as the diaphragm and intercostal muscles. Nevertheless, Liuzijue still holds potential for improving respiratory muscle function. Its unique combination of breathing control and limb movements may provide effective training stimuli for respiratory muscle groups. However, standardized assessment methods for respiratory muscle strength and biomechanical measurement tools are still limited in this field. In recent years, several studies [33,34] have begun to adopt novel biomechanical analysis techniques, such as isokinetic dynamometers and kinematic analysis, to more accurately quantify muscle movement patterns, providing technical possibilities for the precise evaluation of respiratory muscle function. Nevertheless, the mechanisms by which Liuzijue influences respiratory muscle function remain unclear and require further investigation to establish solid scientific evidence.

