9	Multifidus	The junction between the middle $\frac{1}{3}$ and medial $\frac{1}{3}$ of the line from PSIS^d^ to L5^e^

a SENIAM: Surface Electromyography for the Non-Invasive Assessment of Muscles.

b C7: the seventh cervical vertebra.

c ASIS: anterior superior iliac spine.

d PSIS: posterior superior iliac spine.

e L5: the fifth lumbar vertebra.

The sEMG assessment will consist of static and dynamic tests. In the static test, participants will stand quietly while EMG signals are recorded for 5 seconds at rest, at the end of maximal inspiration, and at the end of maximal expiration, with each condition repeated three times at two-minute intervals. The dynamic test will involve a 10-meter walking trial, during which participants are instructed to walk as fast as possible along a corridor while both walking time and EMG signals are recorded simultaneously. The electrode placement for sEMG is illustrated in Figure 3. The sEMG data will be collected in week 0 and week 13.

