**Figure 5. F5:**
[figure not shown]
Gait analysis using a joint motion function testing system. Reflective markers were attached to the participants’ waist, femur, tibia, and foot. Participants walked forward and backward on a treadmill at a speed of 3 km/h for 15 seconds in each direction. Hip, knee, and ankle kinematics, as well as overall gait stability, were evaluated.

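### Unchanged gait at an imposed 3 km/h would not rule out a lower-limb contribution to a 6MWT gain, and the recorded fast 10-m walk time is named as no outcome

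*Protocol article*

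**What the plan says.** Under Exploratory Outcome Measures, Kinematics Test, the protocol article says that gait and plantar pressure are assessed "to investigate lower limb functional improvements following Liuzijue exercise intervention". The treadmill procedure is the same for everyone: "participants first walk forward at a speed of 3 km/h", and "they then walk backward at the same speed, and another 15 seconds of data will be recorded". The Figure 5 legend repeats it: "Participants walked forward and backward on a treadmill at a speed of 3 km/h for 15 seconds in each direction". On timing: "Both gait analysis and plantar pressure assessment will be performed in week 0 and week 13". For the gait part, "The primary outcome measures include joint kinematics of the hip, knee, and ankle, as well as overall gait stability". The plantar part covers foot arch, inversion/eversion curves and, in the accompanying text and the Figure 6 legend, plantar force distribution.

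The Overview of the Exploratory Outcome Measures gives these variables an inferential job. They are to help exclude the possibility that a 6MWT gain comes mainly from better leg function, and they enter the 6MWT model as covariates if they change meaningfully. The Discussion makes a similar claim, that they help remove confounding from muscle adaptation outside the respiratory system.

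Separately, in the dynamic part of the sEMG test, "participants are instructed to walk as fast as possible along a corridor while both walking time and EMG signals are recorded simultaneously". The sEMG data are collected at weeks 0 and 13.

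**The concern.** The question put to the gait and plantar variables is whether leg function could explain a longer 6MWT distance. The 6MWT is a self-paced test at the highest speed the patient can tolerate. The treadmill test fixes the speed in advance, and its variables describe how the patient walks at that speed. The two can diverge: a patient with stronger or more enduring legs may walk further in six minutes while joint angles and stability at 3 km/h stay the same.

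The authors have reason to expect a leg effect. The Introduction says of Liuzijue that it "enhances the strength and endurance of major muscle groups such as the quadriceps and biceps". If the exploratory measures then show nothing, the reasoning in the Overview and the Discussion invites the conclusion that the legs have been excluded and that the gain is respiratory. That would affect the mechanistic reading of a coprimary outcome, though not its estimate. A measurement closer to the question, the timed fast 10-m walk, would meanwhile be on file without a stated role.

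**Working it through.** **1. What each measure can register.** This sets the article's sections side by side.

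| Measure | Where | Speed | Variables named | Walking capacity or leg strength? |
|---|---|---|---|---|
| Treadmill gait | Kinematics Test, Figure 5 | imposed, 3 km/h at both visits | hip, knee and ankle kinematics; stability | no |
| Plantar platform | Kinematics Test, Figure 6 | none stated | arch, inversion/eversion, force distribution | no |
| Isokinetic muscle test (IKMT) | Secondary Outcome Measures | not applicable | trunk flexion and extension, legs stabilised | no, trunk only |
| 6MWT | Primary Outcome Measures | maximum tolerable | distance | yes, whole-body |
| 10-m walk | sEMG, dynamic test | as fast as possible | time recorded; sEMG parameters analysed | yes, but time is not a named outcome |

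The sEMG parameters listed are root mean square, averaged EMG and mean power frequency. Walking time is not among them, nor among the secondary or exploratory outcomes, and the Statistical Analysis section does not mention it.

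**2. The belt speed on the 6MWT scale.** 3 km/h × 0.1 h = 0.3 km = 300 m in six minutes, and 3/3.6 = 0.83 m/s. Anyone whose 6MWT distance exceeds 300 m is tested on the belt below their own six-minute average. The article gives no baseline distance, so the share of patients to whom this applies is not known from it.

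**3. The 6MWT difference as speed.** The 6MWT section cites a minimal important difference of 30 to 54 m; the sample size uses 54 m.
- 30 m / 360 s = 0.083 m/s = 0.30 km/h, which is 10% of belt speed (30/300).
- 54 m / 360 s = 0.15 m/s = 0.54 km/h, which is 18% of belt speed (54/300).

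On the treadmill, change in speed = 3 − 3 = 0 km/h for every patient in both arms, whatever happens to the 6MWT.

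**4. What the 10-m time could register (illustration only).** Change in time = 10/s − 10/(s + Δ), where s is the fast walking speed at week 0 and Δ is 0.083 or 0.15 m/s.
- s = 1.0 m/s: 0.77 to 1.30 s shorter.
- s = 1.2 m/s: 0.54 to 0.93 s shorter.
- s = 1.4 m/s: 0.40 to 0.69 s shorter.

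The speeds s are assumed. So is the premise that fast 10-m speed gains as much as six-minute mean speed; the article supports neither. No power is given, because the article has no SD for 10-m speed.

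**The case against.** The strongest reply is that nothing here is an error. A common belt speed is the sound way to compare joint angles, because it removes speed as a confounder, and the article never claims to measure walking speed on the treadmill. That stands. The point concerns what a null result may be taken to mean.

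A reader might infer that the trial would miss faster walking altogether. It would not: the 6MWT is a primary outcome, is walked at maximum tolerable speed, and would show it.

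A reader might also infer that the gait and plantar variables cannot detect any leg effect. The documents do not support that either. Changes in kinematics, stability or plantar loading can be limb changes without a change in speed, and the plantar platform has no stated imposed speed.

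It can further be said that the silence on 10-m time is a detail for an analysis plan that is not shown, that the sEMG parameter list is worded as open, and that the statistical section has a general provision for other continuous variables. So one cannot say that the time will never be analysed, only that this article gives it no outcome status. What remains is that the article itself assigns the lower-limb question to variables that cannot settle it when they are null.

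Finally, fast 10-m speed is also a whole-body measure. Reporting it cannot by itself separate a limb from a respiratory explanation. That is correct and limits what the fix can claim.

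**Conclusion.** The point holds as one of interpretation and of a missed use of recorded data. With belt speed fixed at both visits and only gait-pattern variables named, an absence of change would not exclude a limb contribution to a 6MWT gain, even one of 30 to 54 m (0.08 to 0.15 m/s). The change in treadmill speed is zero by construction, and that part needs no assumption. The further step, that leg function could improve without altering the named variables, is a judgement about what they measure. It rests on their being pattern measures and on the absence of any leg strength measure among the outcomes.

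No primary estimate, sample size or error rate is affected. How readily the 10-m time would respond is not known from the article.

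**What to change.** 1. Name 10-m maximal walking speed (10 m divided by the recorded time, weeks 0 and 13) as an exploratory functional outcome. Analyse it by ANCOVA adjusted for its week-0 value and report it with a 95% CI beside the 6MWT.
2. State that it is supportive and not limb-specific, and do not use it as a covariate in the 6MWT model. It is measured after randomisation, and adjusting for it would not isolate the respiratory contribution.
3. In the Kinematics Test section, describe the treadmill variables as gait pattern at a standard speed.
4. In the Overview of the Exploratory Outcome Measures and in the Discussion, say that no change in the gait and plantar variables does not rule out a lower-limb contribution to the 6MWT.

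This needs no new test, visit or staff. The cost is wording and one more exploratory comparison, under the false discovery rate adjustment already planned. With 23 of 76 patients enrolled at submission and analysis planned for January 2027, it can be specified before any results are seen.
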